### Ethical considerations

The Chinese PLA General Hospital Ethics Committee approved this study on 12 December 2014 (reference number S2014-119-01). This study complies with the Declaration of Helsinki. Informed consent will be obtained from all participating patients. Upon signing informed consent, patients’ data will be populated as per protocol.

### Details of CCTA examination

#### CCTA examination procedure

CCTA will be performed on a dual-source CT scanner (Somatom Definition Flash, Siemens Healthcare, Forchheim, Germany). All enrolled patients will be instructed in the breath-holding technique before CCTA to minimize breathing artifacts. Three minutes before CCTA, all patients will be given 0.5 mg nitroglycerin sublingually to dilate the coronary artery. The scan range is from the carina or the pulmonary artery segment down to 1 cm below the diaphragm. Electrocardiography is continuously performed throughout the entire examination for each patient. A dual-head power injector (SCT 210, Medrad, USA) and a nonionic contrast medium (Ultravist®, 370 mg I /ml, Schering AG, Guangzhou, China) will be used. The collimation is 2 × 128 × 0.6 mm, the gantry rotation time is 0.28 ms, the slice thickness is 0.6 mm, the tube voltage is 80 to 120 kV (modified using a care kV, Siemens Medical Solutions, Forchheim, Germany), and the tube current is 290 to 560 mAs/rotation (scout-based automatic reference tube current selection – CareDose 4D, Siemens Medical Solutions, Forchheim, Germany). For double flash acquisition, the pitch is 3.4, and for retrospectively ECG-triggered spiral acquisition, the pitch will vary depending on the patient’s heart rate. Total estimated radiation dose for the patient will be recorded.

Patients with a heart rate ≤70 beats/min will be evaluated using double prospective ECG-gated high-pitch CT angiography (double flash mode). For the double flash protocol, the contrast-enhanced CCTA protocol is as follows: a test bolus scan will be performed at the level of the aortic root with administration of 15 ml of contrast medium into the right antecubital vein at a rate of 5.0 ml/s, followed by an injection of 20 ml of saline flush at the same flow rate to obtain a peak enhancement time curve. The double flash acquisition triggered scan time is 4 s after the peak enhancement time. After calculating the triggered scan time, double flash acquisition will be performed by injecting 60 to 90 ml contrast medium at a rate of 5.0 ml/s, immediately followed by 35 ml of 70/30 contrast/saline material mixture and 50 ml saline bolus at the same flow rate. The first scan will begin at 60 % of the R-R interval from the craniocaudal direction. The second scan will be acquired at 30 % of the R-R interval 3 s after the first scan during the same contrast injection time.

Patients with a heart rate >70 beats/min will be evaluated using retrospectively ECG-triggered spiral acquisition. The retrospective protocol is as follows: 60 to 90 ml contrast medium is injected into the antecubital vein at a rate of 5.0 ml/s, immediately followed by 50 ml saline solution at the same flow rate. Bolus tracking is used, and the region of interest is set at the root of the ascending aorta. We will perform the scan with a delay of 5 s after the root of the ascending aorta reaches a threshold of 100 Hounsfield units. For this scan mode, the acquisition is from 30 % to 80 % of the R-R interval.

#### CCTA image post-processing

All CCTA data will be sent to the Syngo Multi-Modality Workplace for post-processing. Two independent experienced observers who are unaware of the patients’ clinical information will evaluate the CCTA data in different modes, including maximum intensity projection, volume rendering, curved-planar reconstructions, and the original transaxial images. Disagreements in data analysis between the two readers will be resolved by consensus reading.

#### Epicardial adipose tissue quantification

The EAT volume will be measured by two experienced radiologists using the same sets of images acquired for the CCTA. The radiologists will be blinded to the purpose of the study, clinical characteristics and patients’ anthropometric data.

The EAT volume is defined as the total amount of adipose tissue deposited between the surface of the heart and the visceral pericardium. The region of interest in measuring the EAT volume includes the heart and the surrounding EAT. By manually tracing the epicardium contours in the axial slices from the bifurcation of the pulmonary artery to the diaphragm, the EAT volume is analyzed. The pericardium contour is traced every 10 mm, from the lower visible level of the pulmonary artery bifurcation until the top level of the pulmonary valve, for every 20 mm until the first slice where the diaphragm becomes visible, and for every 10 mm from this point until the last slice where the pericardium is still visible [31]. The pericardium contour is manually outlined by the radiologists, and then the software (Syngo Volume, Siemens Medical Solutions) automatically calculates the total EAT volume. Computed tomography attenuation ranging from −195 to 45 Hounsfield units is applied to isolate the EAT from other tissues. Mediastinal adipose tissue and pericardial adipose fat (fat deposit outside the visceral pericardium and on the external surface of the parietal pericardium) are excluded from the analysis. For the assessment of interobserver agreement, we will randomly select 50 patients, and all EAT measures will be assessed by two experienced radiologists blinded to the other radiologist’s measurements.

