### Treatment of epicardial adipose tissue and coronary atherosclerosis

There are ample studies exploring the progression of coronary atherosclerosis following pharmacological manipulation. At the time of writing, the use of statins is recognized as an effective treatment; statins can result in decreases in plaque and necrotic core volume, and can also significantly reduce the progression of low attenuation plaque (<30 Hounsfield units) and non-calcified plaque [8, 9]. Other drugs, such as dipeptidyl-peptidase 4 inhibitors [10], a PPARγ agonist (pioglitazone) [11], atorvastatin plus ezetimibe [12], olmesartan [13], have also been reported to have antiatherosclerotic effects, although the effects have not been verified by large-scale studies. As studies show that EAT volume is associated with plaque progression and cardiovascular adverse events, treatments aimed at reducing EAT volume may finally achieve an antiatherosclerotic, preventive effect. However, at the time of writing, limited studies have aimed at reducing both EAT and plaque volume to achieve an antiatherosclerotic effect. A serial coronary computed tomography angiography (CCTA) study recently indicated that intensive statin therapy can reduce the EAT volume of Europeans, but the study failed to demonstrate a relationship among EAT volume reduction, coronary atherosclerosis progression and clinical prognosis [14]; moreover, intensive statin therapy might not be appropriate for Asians. The epidemiological studies and clinical researches show that Asians may have poorer tolerability and safety to intensive statins than white people, owing to genetic differences (variants in structure or polymorphisms) in pharmacokinetics and pharmacodynamics properties [15–17]. It has been claimed that polymorphic variants in cytochrome P450 (CYP450) families that were associated with statin metabolism might result in varying rates of metabolic clearance. CYP450 2C19 slow metabolizer phenotype was reported to be present in approximately 16 % of Asians compared with only about 3 % of white people [18]. Polymorphic variants in the predominant CYP450 isoform, CYP450 3A4, were reported to be associated with a functional decrease in the enzyme’s activity in dyslipidemic Chinese patients [19]. The HPS2-THRIVE study recently also indicated that, using same-dose statin treatment, an excess of increased alanine aminotransferase was seen mainly among Chinese patients (more than three consecutive values above the upper limit of normal of 0.24 %/year compared with 0.02 %/year in Europe) [20]. Moreover, the morbidity of chronic hepatitis B was high in china with nearly 90 million infections. For these reasons, intensive statin therapy may result in higher hepatotoxicity in Asian populations than in white populations, so low- to moderate- dose statin therapy might be more appropriate for Asian populations [15, 16]. Subjects who undergo weight loss exercise, bariatric surgery, or low-dose aspirin therapy can also reduce EAT volume or inflammation, but the effects are weak and these treatments cannot achieve good results in patients with coronary atherosclerosis progression [21–24]. Our aim is to find a drug that reduces EAT volume while inhibiting the progression of coronary atherosclerosis.

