### Study outcomes

The primary outcome measures are coronary atherosclerosis progression and EAT volume changes, as detected by CCTA at 12 months.

The secondary outcome measures includeThe relationship between coronary atherosclerosis and EAT;Serum levels of blood lipids, glucose, circulating surrogate markers of atherosclerotic inflammation including high-sensitivity C-reactive protein, IL-6, MCP-1, TNF-α, and MMP-9, individual circulating surrogate markers of endothelial function including NO and ET-1, and individual circulating surrogate markers of adipose tissue inflammation and metabolism including adiponectin and leptin at baseline and after 6 and 12 months.

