### Sample size calculation

This trial is an open-label randomized clinical trial, so patients will randomly be assigned to olmesartan medoxomil or conventional antihypertensive medication groups (1:1 ratio). The purpose of this study is to verify that olmesartan medoxomil is effective in the treatment of coronary atherosclerosis progression and EAT volume reduction in patients with coronary atherosclerosis detected by CCTA. We also want to elucidate the relationship between coronary atherosclerosis and EAT. The mechanism by which olmesartan medoxomil inhibits coronary atherosclerosis progression will be studied by detecting the serum levels of blood lipids, glucose, circulating surrogate markers of atherosclerosis inflammation including high-sensitivity C-reactive protein, IL-6, MCP-1, TNF-α, and MMP-9, circulating surrogate markers of endothelial function, including NO and ET-1, and circulating surrogate markers of adipose tissue inflammation and metabolism, including adiponectin and leptin.

Studies on coronary atherosclerosis progression rate have had differing results. The combined results of multiple studies indicate that the conventional mean coronary atherosclerosis progression rate is about 30 % [33–35]. We hypothesize that additional olmesartan medoxomil use will reduce the coronary atherosclerosis progression rate to 13 % [36–40]. Using double-side inspection, α = 0.05, β = 0.2, we calculate a total sample size of 176 cases; considering the expected loss to follow-up to be 10 %, the number of cases to be included should be at least 176 × (1 + 10 %) = 194. Therefore, we aim for 97 cases of each group.

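### As printed, the EAT attenuation window runs up to +45 HU, so it admits non-fat voxels and does not isolate a fat volume for a primary outcome

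*Protocol article*

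**What the plan says.** The Protocol article fixes the measurement in the section Epicardial adipose tissue quantification.

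- Target: "The EAT volume is defined as the total amount of adipose tissue deposited between the surface of the heart and the visceral pericardium".
- Images: the measurement is made "using the same sets of images acquired for the CCTA". The section on the CCTA examination procedure shows that these are contrast-enhanced.
- Region: "The region of interest in measuring the EAT volume includes the heart and the surrounding EAT".
- Calculation: once the contour has been drawn by hand, "the software (Syngo Volume, Siemens Medical Solutions) automatically calculates the total EAT volume".
- Separation of fat from non-fat: "Computed tomography attenuation ranging from −195 to 45 Hounsfield units is applied to isolate the EAT from other tissues".
- Other exclusions: mediastinal fat and fat outside the pericardium are left out because of where they lie.

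No other section gives a different EAT threshold. Under Study outcomes the article says: "The primary outcome measures are coronary atherosclerosis progression and EAT volume changes, as detected by CCTA at 12 months". EAT volume is also a term in the logistic regression under Statistical analysis, and its relationship with atherosclerosis is listed as a secondary outcome. The Background gives one attenuation value for a non-fat tissue, where it mentions "low attenuation plaque (<30 Hounsfield units".

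**The concern.** The lower limit carries a minus sign and the upper limit does not. The Hounsfield scale sets water at 0, and adipose tissue lies below it. A window meant to pick out fat should therefore end below 0, and this one ends 45 HU above it. The definition (adipose tissue only) and the rule that implements it contradict each other within one section.

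At stake is the meaning of a primary outcome. If the printed limit is the one in use, a change in pericardial fluid, or in the number of partial-volume voxels at tissue borders, can be read as a change in EAT. Some non-calcified plaque in the epicardial arteries could be counted as EAT too, which might touch the planned analysis of EAT against plaque progression.

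**Working it through.** The window is a fixed setting, so no formula reproduces it. The check is whether it can do what the section says it does.

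**1. Does anything else remove non-fat tissue?** The contour does not, because the region contains the heart. The exclusions by location remove fat in the wrong place, not non-fat tissue. Only the attenuation window separates fat from non-fat.

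**2. What does the window contain?**

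- Width as printed: 45 − (−195) = 240 HU.
- Part at or above water: 45 / 240 = 18.75 %.
- Width if the limit were −45 HU (an assumption; the value is not in the document): −45 − (−195) = 150 HU.
- Difference: 240 − 150 = 90 HU, or 90 / 240 = 37.5 % of the printed window, lying from −45 to +45 HU around water.
- The Background's plaque category below 30 HU overlaps the window from −195 to 30 HU.

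**3. What share of each tissue's voxels would be counted as EAT?** For a normal attenuation distribution with mean m and SD s, the share below upper limit U is Φ((U − m)/s) − Φ((−195 − m)/s). All means and SDs here are assumptions; the document gives none.

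| Tissue (m, s in HU) | U = +45 | U = −45 |
|---|---|---|
| Fat (−100, 25) | 100 % | 98.6 % |
| Water (0, 20) | 98.8 % | 1.2 % |
| Fluid (15, 20) | 93.3 % | 0.1 % |
| Non-fat tissue (30, 20) | 77.3 % | 0.0 % |
| Non-fat tissue (40, 20) | 59.9 % | 0.0 % |
| Enhanced tissue (100, 25) | 1.4 % | 0.0 % |

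For water, for example, 45/20 = 2.25 gives Φ = 0.988, and −45/20 = −2.25 gives 0.012. Under these assumptions the printed limit takes in most fluid and low-attenuation tissue, and a −45 HU limit would exclude nearly all of it while losing about 1.4 % of fat voxels. Well-enhanced tissue is excluded either way.

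**4. Can this be turned into a bias in the outcome?** That needs the volume of non-fat tissue near the window and its change over 12 months, and the document gives neither. The sample size does not help. With 30 % against 13 % progression, two-sided α = 0.05 and power 0.80, the unpooled formula gives (1.960 + 0.842)² × (0.30 × 0.70 + 0.13 × 0.87) / 0.17² = 87.75. That is 88 per arm, or 176 in total, as stated ("Using double-side inspection, α = 0.05, β = 0.2, we calculate a total sample size of 176 cases"). No EAT effect, SD or power enters the calculation.

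**The case against.** The strongest reply is that this is a misprint. If the software used a negative limit throughout, the measured volumes are sound and only the text is wrong. Nothing in the document shows that +45 HU was the operating preset. This stands as to consequences. It does not excuse the text, because this sentence is the only rule that turns a contour into a fat volume, and someone applying the article literally would use +45 HU. The minus signs on −195 HU and on the −80 °C storage temperature under Biomarkers are printed, so a general loss of minus signs is not evident.

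Three stronger readings are tempting, and the document does not support them.

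- *The trial loses a definite amount of power on EAT.* The document states no EAT effect, SD or power, so both the starting power and any added variance would have to be invented. In addition, if measured volume is fat plus non-fat, the change is Δfat + Δnon-fat, and non-fat volume that is stable within a patient cancels from an absolute change. It would not cancel from a percentage change, or where EAT volume enters a model as a level. That shows where a problem could arise, not how large it is.
- *The two primary outcomes become artificially correlated.* The figure of 30 HU comes from a Background sentence about earlier statin studies and is not this trial's plaque rule. Progression is defined by diameter stenosis or minimal luminal diameter, so plaque voxels counted as EAT do not enter that outcome directly. An induced association is possible but not shown.
- *All soft tissue is counted as fat.* The images are contrast-enhanced, so well-enhanced blood and myocardium would mostly fall outside the window. The contamination is confined to fluid, vessel wall, low-attenuation plaque, poorly enhanced tissue and partial-volume voxels.

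It is also fair to say that −45 HU is an inference. The document supports only that a positive limit is wrong for isolating fat.

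**Conclusion.** The rule is wrong as written. A window of −195 to +45 HU contradicts the adipose-only definition in the same section, nothing else in the method compensates for it, and it defines a primary outcome. This conclusion rests on the definition of the Hounsfield scale and the article's own text, not on the assumed distributions.

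The size is known only for the setting itself: 45 HU of the window lie above water, and the window is 90 HU wider than it would be if a minus sign was lost. The voxel shares illustrate the direction and rest on assumed means and SDs. Whether any volume was measured with +45 HU, and how far EAT change would then be off, cannot be determined from the document. A probable sign error in a primary-outcome setting still needs correcting, because the text alone does not tell a reader what was measured.

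**What to change.** Correct the upper limit in Epicardial adipose tissue quantification to a negative value, presumably −45 HU, and cite its source. Confirm the value first against that source and against the preset in the volume software. State that the same window applies at baseline and at 12 months.

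If any scan has been read with +45 HU, recalculate its EAT volume with the corrected window. The article does not say whether contours are saved. If they are, only the automatic step has to be repeated; if not, the affected scans need tracing again.

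The cost is one corrected figure and a check of the preset, plus the repeat calculation for affected scans if the preset was wrong. The sample size is unaffected, because the window does not enter it.

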#### Definition of coronary atherosclerosis plaque progression

We will use QAngio CT post-processing software (QAngioCT Research Edition version 2.1.0, Medis Medical Imaging Systems, Leiden, the Netherlands) to evaluate all CCTA data. All three vessels will be assessed in each patient using the 15-segment American Heart Association model for coronary segment classification [32]. Only segments with a diameter ≥2.0 mm and without stent implantation will be considered for analysis. Parameters including minimal lumen diameter, percent diameter stenosis, minimum lumen area, plaque burden, plaque volume, vascular remodeling index, plaque type classification (calcification, necrosis, fiber, and fiber lipid plaques) based on segments will be analyzed using QAngio CT post-processing software.

Coronary atherosclerosis progression is defined as ≥10 % diameter reduction or progression of a pre-existing coronary stenosis or ≥0.2 mm reduction or progression of the minimal luminal diameter in the lesion [30].

### Medication intervention and control protocols

All patients should accept lifestyle interventions and conventional anti-atherosclerosis treatment. The low-density lipoprotein cholesterol level should be controlled below 100 mg/dl, and the blood pressure should be controlled below 140/90 mmHg.

In the olmesartan medoxomil group, the usual recommended starting dose of olmesartan medoxomil is 20 mg once daily when used as monotherapy in patients who are not volume-contracted. For patients requiring further reduction in blood pressure after 2 weeks of therapy, the dose of olmesartan medoxomil may be increased to 40 mg. Doses above 40 mg do not appear to have a greater effect. Twice-daily dosing offers no advantage over the same total dose given once daily.

In the control group, any antihypertensive medication alone or in combination, including calcium channel blockers, diuretics, beta blockers, or other antihypertensive medication except angiotensin-converting enzyme inhibitors or angiotensin II receptor blockers can be used. The drug dose must be individualized. The patients should take the antihypertensive drugs according to the doctors’ recommendations.

### Study outcomes

The primary outcome measures are coronary atherosclerosis progression and EAT volume changes, as detected by CCTA at 12 months.

The secondary outcome measures includeThe relationship between coronary atherosclerosis and EAT;Serum levels of blood lipids, glucose, circulating surrogate markers of atherosclerotic inflammation including high-sensitivity C-reactive protein, IL-6, MCP-1, TNF-α, and MMP-9, individual circulating surrogate markers of endothelial function including NO and ET-1, and individual circulating surrogate markers of adipose tissue inflammation and metabolism including adiponectin and leptin at baseline and after 6 and 12 months.

### Biomarkers

Two 10-ml samples of blood will be collected from the antecubital vein by a trained nurse for each individual. Fasting blood samples will be obtained between 7:00 a.m. and 12:00 noon to control for possible diurnal variations. Blood samples will be centrifuged at 4 °C and 3,000 rpm for 15 min. The serum will be sampled and stored at −80 °C until analysis. Traditional cardiovascular blood risk markers, including fasting blood glucose, triglycerides, total cholesterol, and high- and low-density lipoprotein cholesterol will be assessed. The following proinflammatory markers will be assessed: high-sensitivity C-reactive protein, IL-6, TNF-α, MCP-1, and MMP-9. In addition, NO and ET-1 will be measured, to assess endothelial function. Markers of adipose tissue inflammation and metabolism, including adiponectin and leptin, will also be assessed. These markers will be measured at baseline and 6 and 12 months after treatment.

### Follow-up

Clinical follow-up will take place at 1 month (±1 week), 3 months (±2 weeks), 6 months (±2 weeks), 9 months (±30 days), and 1 year (±30 days) by clinical visit or phone interview.

At baseline and 6-month (±2 weeks) and 1 year (±30 days) follow-ups, all patients will provide venous blood for detection of blood lipids, glucose, high-sensitivity C-reactive protein, IL-6, MCP-1, TNF-α, NO, ET-1, MMP-9, adiponectin, and leptin.

At 1 year (±30 days) follow-up, all patients will undergo CCTA (with QAngio CT post-processing software).We anticipated a patient drop-out rate of 10 %.

